## Abstract

**Introduction:**

Participation in bowel cancer screening is lower in regions where there is high ethnic diversity and/or socioeconomic deprivation. Interventions, such as text message reminders and patient navigation (PN), have the potential to increase participation in these areas. As such, there is interest in the comparative effectiveness of these interventions to increase bowel cancer screening participation, as well as their relative cost-effectiveness.

**Methods and analysis:**

This study will use a three-arm randomised controlled trial design to compare the effectiveness and cost-effectiveness of text message reminders and PN to increase the uptake of bowel cancer screening in London. Participants will be individuals who have not returned a completed faecal immunochemical test kit within 13 weeks of receiving a routine invitation from the London bowel cancer screening hub. Participants will be randomised (in a 1:1:1 ratio) to receive either (1) usual care (ie, ‘no intervention’), (2) a text message reminder at 13 weeks, followed by repeated text message reminders at 15, 17 and 19 weeks (in the event of non-response) or (3) a text message reminder at 13 weeks, followed by PN telephone calls at 15, 17 and 19 weeks in the event of non-response. The primary endpoint will be participation in bowel cancer screening, defined as ‘the return of a completed kit by week 24’. Statistical analysis will use multivariate logistic regression and will incorporate pairwise comparisons of all three groups, adjusted for multiple testing.

**Ethics and dissemination:**

Approvals to conduct the research have been obtained from University College London’s Joint Research Office (Ref: 150666), the Screening Research, Innovation and Development Advisory Committee (‘RIDAC’, Ref: 2223 014 BCSP [name]), the Health Research Authority (Ref: 22/WM/0212) and the Confidentiality Advisory Group (Ref: 22/CAG/0140). Results will be conveyed to stakeholders, notably those managing the screening programme and published in peer-reviewed journals/presented at academic conferences.

**Trial registration number:**

ISRCTN17245519

STRENGTHS AND LIMITATIONS OF THIS STUDYThis is a randomised controlled trial using individual-level data, as opposed to area-level data, increasing the studies ability to attribute increases in uptake, directly to the intervention.The study focuses on ethnically diverse areas, increasing the generalisability of the research to other parts of the UK.The study relies on general practices to consent to the study, which introduces an element of self-selection bias.The text message reminders will be delivered in English, which may limit the equitability of the intervention and undermine its effectiveness.Not every participant will have a mobile telephone number, which could undermine results. The study will use intention-to-treat analysis to compare individuals across groups, who have a mobile number recorded on the general practitioner system.

## Introduction

 Colorectal cancer (CRC, also known as ‘bowel cancer’) is a leading cause of cancer-related mortality in Europe.^1^
^2^ Several large randomised controlled trials (RCTs) have shown that biennial faecal immunochemical test (FIT) screening can improve CRC outcomes by detecting cases early.^3^ In light of this, many countries, across Europe, have implemented programmes based on the test.^4^

England is one such country that has implemented an FIT-based programme. In England, the National Health Service (NHS) began offering biennial FIT screening to adults aged 60–74 years in 2019. The screening programme, referred to as the NHS Bowel Cancer Screening Programme (BCSP), is delivered through five national hubs, which send kits to patients registered with a general practice within their respective regions. The delivery of invitations is an automated and centralised process in which information held by the patient’s general practice, including their date of birth, name and address, is shared with the BCSP to facilitate the process. Date of birth is used to identify individuals who are eligible for screening, while name and address are used to send the invitations to those individuals. An age extension to the programme is currently underway, with the aim of all adults aged 50–59 receiving an invitation by 2025. At the time of writing, the programme has been extended to include adults aged 54–59 years.

As with any screening programme, achieving the public health benefits of bowel cancer screening is highly dependent on high and equitable uptake. However, despite being offered free at the point of use, in England, uptake of FIT screening is suboptimal and marked by stark social, regional and ethnic inequalities.^5^
^6^ Uptake is particularly low in London, where there is an eight-percentage point differential with the national average (ie, 62.1% vs 70.3% (2021/2022)).^5^ This is true despite several interventions having been shown to reduce inequalities and having been implemented as a result. For example, an enhanced reminder letter, sent to non-responders, was previously shown to disproportionately increase uptake among individuals living in more socioeconomically deprived areas and was embedded in the programme as a result.^7^ Two interventions, which are not currently implemented, but are being considered, are text-message reminders and patient navigation (PN).^8 9^

Text message reminders, sometimes referred to as short messaging system reminders, are of particular interest to researchers seeking to reduce inequalities in screening, due to their relatively low cost, non-confrontational nature and the ubiquity of mobile telephones among the adult population (a recent survey by the Office for National Statistics indicated that over 95% of adults living in the UK own a mobile phone).^10^ A systematic review of text message reminders in cancer screening found them to be effective at improving participation rates by up to 15%, with the effectiveness of the reminder being contingent on a number of factors, including the content of the message and the number of messages sent.^11^

PN is another telephone-based intervention, one which involves the provision of personal support, from a trained ‘navigator’, to help patients overcome personal or system-related barriers to healthcare.^12^ As with text message reminders, PN is an intervention that has been of interest to researchers seeking to reduce inequalities in screening, due to the potential to deliver culturally tailored information to individuals whose main language is not English (eg, first-generation migrants). Previous studies have shown that such navigation can increase screening participation.^12^ Indeed, a review and meta-analysis conducted by Nelson *et al* showed a 64% increase in participation in colorectal, breast and cervical screening participation, with a PN intervention.^13^

While strong evidence indicates that both text message reminders and PN are effective, and the aggregate data indicate that PN results in larger effect sizes, few studies have directly compared the effectiveness and cost-effectiveness of these interventions with one another. As such, further research is needed to determine the most effective and cost-effective approach to promoting bowel cancer screening uptake and reducing inequalities in screening. The aim of this study, therefore, is to directly compare these two interventions so as to identify the most effective and cost-effective means to promote uptake of FIT screening in London.

## Methods and analysis

### Study design

This study will be an RCT with three parallel groups. Adults aged 54–74 years, who are registered with a participating general practice, and have not taken part in bowel cancer screening, within 13 weeks of receiving their invitation, will be randomised in equal proportions (1:1:1), to receive either:

No intervention.A text-message reminder, followed by additional text-message reminders at 15, 17 and 19 weeks (if there is no response).A text-message reminder, followed by PN calls at 15, 17 and 19 weeks (again, if there is no response).

See online supplemental file 1, figure 1 for an overview of the study design/Consolidated Standards of Reporting Trials diagram.

**Figure 1 F1:**
[figure not shown]
CONSORT diagram detailing the study design. Blue=standard care processes; Green=project-specific processes carried out by London Bowel Cancer Screening Hub; Orange=project-specific processes carried out by iPlato. CONSORT, Consolidated Standards of Reporting Trials; PN, patient navigation.

### Participants and eligibility criteria

Participants will be men and women, aged 54–74 years, who have not returned a bowel cancer FIT screening kit, within 13 weeks of delivery and are registered with a participating general practice located within the London Boroughs of Brent, Ealing, Lambeth, Lewisham, Redbridge and Barking and Dagenham (preselected based on their low screening uptake and CRC survival rates—see table 1). We are deliberately targeting individuals at 13 weeks, as their screening episode is technically closed at this point, and individuals are considered ‘responders’ or ‘non-responders’, depending on whether they have completed the test kit. This means that we are able to focus interventions on non-responders (ie, those who are most likely to benefit from them) and reduce costs by avoiding delivering the interventions to those who would take part without intervention.

**Table 1 T1:** Study setting characteristics: iPlato sign-up, FIT screening uptake and age-standardised mortality rates in London

CCG*	iPlato Sign-up* % (n/n)	FOBt/FIT screening uptake 2019† % (n/n)	FOBt/FIT screening uptake 2019† (compared with London)	Mortality rate† (per 100 000 persons)	Mortality rate† (compared with London)
Brent(Northwest)	94%(49/52)	47.04%(17 364/36 921)	Worse	10.1	Similar
Ealing(West)	88%(66/75)	50.54%(20 782/41 116)	Worse	9.5	Similar
Redbridge(East)	83% (35/42)	50.07%(16 743/33 436)	Worse	8.5	Similar
Barking and Dagenham(East)	97%(33/34)	44.90%(8032/18 491)	Worse	14.8	Worse
Lewisham(South)	94%(33/35)	48.84%(13 524/27 695)	Worse	14.7	Worse
Lambeth(South)	95%(39/41)	45.98%(13 327/28 984)	Worse	11.3	Similar
Total	91.40%(255/279)	48.98%(89 772/1 86 643)			

* Data from iPlato.

† Data from Public Health England—Public Health Profiles.

CCGClinical Commissioning GroupFITfaecal immunochemical test

Exclusions will be made according to ‘type-2 objector’ status, which is defined as: ‘a request, expressed by a registered patient, logged with a general practitioner (GP) practice, to indicate that personal identifiable information relating to them should not be disseminated or published by NHS Digital’.^14^

### Participant recruitment

Eligible adults will be identified on a weekly basis, until the sample size requirement is achieved (approximately 4–8 weeks), by the London Bowel Cancer Screening Hub, which will use data stored on the bowel cancer screening system to identify individuals based on their bowel cancer screening status (ie, whether they are a non-responder) and bowel cancer screening invitation date (ie, to confirm when they were invited for screening, and whether they are a ‘new’ non-responder).

### Consent

To ensure the ecological validity of the study, consent will not be obtained from individual participants. Instead, GPs will provide a proxy consent for iPlato (the text message and PN provider—see below) to contact them on their behalf, using the telephone numbers of patients stored on their clinical system. Potentially eligible participants will be notified that a study is taking place, through patient notification posters, which will be displayed at participating general practices. These posters will be displayed prior to, and throughout, the study, and will inform individuals they can withdraw by notifying reception. At the end of the study, participants will be sent a letter, by the London bowel cancer screening hub, debriefing them that they were involved in a study and the reasons why (see online supplemental appendix 1).

### GP recruitment

GPs will be recruited to the study via email. They will receive an information sheet and consent form from the Joint Screening and Immunisation Lead for Cancer Screening in London ([name], NHS England), which they will be required to sign and return to the chief investigator ([name], UCL and University of Surrey), in order to participate in the study. Based on previous studies testing similar interventions and recruitment strategies,^15 16^ we expect to recruit ~50% of practices within the London Boroughs of Brent, Ealing, Lambeth, Lewisham, Redbridge and Barking and Dagenham.

### Interventions

As described in Study design section, individuals will be randomised to receive either:

no intervention (‘usual care only’).A text-message reminder, 13 weeks after the invitation, with additional text-message reminders at 15, 17 and 19 weeks if there is no response (Individuals in the patient navigation group will receive a text message reminder at 13 weeks, in addition to patient navigation calls at 15, 17 and 19 weeks. This will allow iPlato (the company delivering the patient navigation telephone calls) to confirm which individuals’ telephone numbers are active, and call only those individuals who have an active telephone number. This will reduce the cost of the intervention, by ensuring only those with an active number are contacted (ie, less time spent attempting to contact individuals whose numbers are no longer valid/UpToDate)). (‘text message reminder(s)’).A text-message reminder, 13 weeks after the invitation, followed by PN calls at 15, 17 and 19 weeks if there is no response (‘text message reminder+PN telephone call(s)’).

#### Text message reminders

The text message reminders (SF 2, figure 2) for both intervention groups will remind recipients that they have not yet completed their kit, and that they are able to request a new one (should they wish to take part), via Freephone, from the BCSP. The following link, which provides relevant information in different patient languages, will be included in the text message reminder, to support individuals whose first language is not English: www.cancerchampionsgm.org.uk/wp-content/uploads/sites/2/2021/10/Bowel-Screening-%E2%80%93-Language-Support.pdf..

**Figure 2 F2:**
[figure not shown]
Text message reminder script.

Instructions on how to opt-out of further contact for the study, and wider research, will also be provided.

The decision to include the option for recipients to request a new test kit was based on previous research exploring reasons for not completing an FIT screening kit, which documents one of the reasons as having ‘misplaced’ or ‘lost’ the kit.^17^

#### PN telephone calls

The PN telephone calls will similarly remind recipients that they have not yet completed their kit and will provide them with the opportunity to request a new kit (should they wish to take part) via the London Bowel Cancer Screening Hub. In addition, the PN telephone calls will elicit barriers to participation, which the navigator will provide advice on, to support the individual in completing the test (see online supplemental appendix 2 for a copy of the PN script that will be used for this study). A record of all calls, and the barriers discussed, will be documented, to elucidate which barriers are successfully addressed by the PN calls (this will be confirmed by request and completion of a test kit).

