### Data collection

At the end of the study (‘week 24’), the London Bowel Cancer Screening Hub will extract the following data on study participants, from the available bowel cancer screening system: sex, age, index of multiple deprivation quintile (derived from the participant’s postcode), adequate completion (ie, ‘kit returned’ (yes/no)) and bowel cancer screening result (normal/abnormal). The data will then be anonymised and analysed by a data analyst at the London Hub.

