### Sample size calculation

For the control, text-message reminder and PN groups, we anticipate that 1.0%, 3.2% and 15.0% of participants (respectively) will complete a kit by week 24 (this is based on data provided by NHS England, as well as previous research conducted with the London BCSP) (Personal Communication). We subsequently designed our sample size calculation to provide sufficient power to allow us to test for the smallest possible difference, between any two groups, of 2.2 percentage points (ie, 1% in the control vs 3.2% in the text message reminder group). As three separate comparisons are planned for the main analysis (control vs text message reminders; control vs PN; text message reminders vs PN), we used an adjusted significance level (ie, 0.015) for our sample size calculation (as per the Bonferroni correction method, which takes into account inflation of the alpha statistic, caused by multiple comparisons), so as to maintain an overall 5% probability for any false positive result. To achieve 80% power at this level, our study requires 901 subjects per group (2703 recruits in total; see table 2 for details).

**Table 2 T2:** Sample size calculations

	P1	P2	Alpha*	Beta	n (per arm)	n (total)
Comparison 1						
No intervention† versusText-message reminders‡	0.0098	0.0318	0.015	0.2	901	2703
Comparison 2						
No intervention† versusText-message reminder+PN§	0.0098	0.1334	0.015	0.2	92	276
Comparison 3						
Text-message reminders versusText-message reminder+PN§	0.0318	0.1334	0.015	0.2	156	468

* An adjusted Alpha of 0.015 has been used to account for inflation of the statistic, resulting from multiple comparisons (ie, 0.05 / 3).

† Expected uptake based on 2019 data for FOBt/FIT, 13-24 weeks after invitation (PHE, personal communication).

‡ Expected uptake for text reminders based on the results of the service evaluation for the Southeast London breast screening service (iPlato, personal communication).

§ Expected uptake for text reminders and patient navigation based on the results of the service evaluation for the Southeast London breast screening service (iPlato, personal communication).

FITfaecal immunochemical test

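### Requesting and completing a kit cannot confirm that a navigation call resolved a barrier; completion by barrier should be reported as description only

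*Protocol article*

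**What the plan says.** The Protocol article, PN telephone calls, describes a call with several parts. It reminds the person that the kit is outstanding, gives an opportunity to request another, and also elicits barriers and offers advice on them. Calls and barriers are logged "to elucidate which barriers are successfully addressed by the PN calls (this will be confirmed by request and completion of a test kit"). That sentence gives both an aim (which barriers the calls succeed in addressing) and a criterion for deciding it (request plus completion).

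On timing, the Interventions section states: "Individuals in the patient navigation group will receive a text message reminder at 13 weeks, in addition to patient navigation calls at 15, 17 and" (the last call falls at week 19). The calls are made only to those who have not responded. According to Text message reminders, the text itself already tells recipients how to request a new kit. No barrier information is described for the control or text-only arms.

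Under Sample size calculation, the expected completion is given as follows: "For the control, text-message reminder and PN groups, we anticipate that 1.0%, 3.2% and 15.0% of participants (respectively) will complete a kit by week 24". Table 2 in the same section uses 0.0098, 0.0318 and 0.1334.

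**The concern.** The criterion reads an outcome after a call as proof of what the call did. Three features of the design stand in the way.

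- **No comparator at barrier level.** Barriers are elicited in one arm, from the people who are called. Nobody with the same recorded barrier goes without a call. The randomised comparison of text with text plus PN estimates the effect of the whole package, not of resolving a particular barrier.
- **A bundled call.** Even a completion that the call truly caused may be due to the reminder or the offer of a kit rather than to the advice on the barrier.
- **Background completion.** The protocol's own planning rates allow for completion with no call, and the PN arm has a text two weeks before the first call.

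The criterion also errs in the other direction. Someone whose concern was resolved, and who then completed the original kit without asking for another, does not meet it.

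What is at stake is a causal statement about individual barriers, reported beside a randomised result, that the data cannot bear.

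**Working it through.** **1. Are the Table 2 rates the ones the trial was planned on?** Inputs (Sample size calculation): two-sided alpha 0.015, power 80%, equal groups. Sidedness is not stated, but two-sided reproduces the figures. The formula, with pooled variance and no continuity correction, is

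n = [z(1−α/2)·√(2p̄(1−p̄)) + z(0.80)·√(p1(1−p1) + p2(1−p2))]² / (p1 − p2)²

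- 0.0098 v 0.0318: n = 901
- 0.0098 v 0.1334: n = 92
- 0.0318 v 0.1334: n = 156

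All three match Table 2, so 0.0098, 0.0318 and 0.1334 are the rates behind the 901 per arm. The text gives 15.0% for PN where the table has 13.34%, so both are carried below.

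**2. Share of all PN-arm completions also expected with texts alone** = text rate / PN rate.

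- Table 2: 0.0318/0.1334 = 23.8%. At 901 per arm, 901 × 0.0318 = 28.7 of 901 × 0.1334 = 120.2, or about 29 of 120.
- Text: 3.2/15.0 = 21.3%. At 901 per arm, 28.8 of 135.2, or about 29 of 135.
- Against no intervention: 0.98/13.34 = 7.3%, or 1.0/15.0 = 6.7%.

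**3. Does that ratio apply to the people who meet the criterion?** No. They are a narrower group: reached by phone, barrier discussed, kit requested, kit completed. People who respond before week 15 are not called, and people who are not reached have no barrier recorded. The document gives neither the timing of returns nor the share reached, so the figures below rest on assumptions. Let t be the text rate, p the PN rate, f the share of text-only completions that fall before week 15, and r the share reached, with unreached people completing at the text rate. Then

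share = r·t·(1−f) / [(p − t) + r·t·(1−f)]

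| Assumed f | Assumed r | Table 2 rates | Text rates |
|---|---|---|---|
| 0 | 1 | 23.8% | 21.3% |
| 0.25 | 1 | 19.0% | 16.9% |
| 0.50 | 1 | 13.5% | 11.9% |
| 0.75 | 1 | 7.3% | 6.3% |
| 0 | 0.8 | 20.0% | 17.8% |
| 0 | 0.6 | 15.8% | 14.0% |
| 0 | 0.4 | 11.1% | 9.8% |
| 0.50 | 0.6 | 8.6% | 7.5% |

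For example, with Table 2 rates, f = 0.50 and r = 0.6: 0.6 × 0.0318 × 0.5 = 0.00954, and 0.00954/(0.1016 + 0.00954) = 8.6%.

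The first row is a ceiling only if calls deter nobody and every completion caused by a call meets the criterion. If some of those people use the original kit and make no request, the share could be higher.

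**4. Limits of the comparison rate.** The 3.18% is for a schedule of up to four texts, whereas the PN arm has one text and then calls. No rate is given for one text without calls. Both intervention rates come from a breast screening service evaluation; for PN the Table 2 footnote reads "Expected uptake for text reminders and patient navigation based on the results of the service evaluation for the Southeast London breast screening service".

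**The case against.** The strongest reply is that this is one parenthesis about a process record. The barrier log is neither the primary nor the secondary outcome (Outcomes), and Data analysis plans no test of it. The policy question in the Dissemination plan rests on the randomised comparison, which is unaffected. All of that stands, and it sets the severity. It does not rescue the sentence, which states a criterion and a causal conclusion rather than leaving them to a later document.

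Three stronger readings are tempting, and the document does not support them.

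- **A reader might infer that about a quarter of the logged successes would have happened anyway.** The 24% is a ratio over everyone in the PN arm who completes, not over called people with a barrier recorded. It also uses one of the two stated PN rates and a comparison arm with more texts.
- **A reader might infer that the criterion ranks barriers wrongly, flattering a mislaid kit over, say, fear of the result.** This is plausible, because a person with a lost kit has to request one. But no completion rate by barrier is given, and the protocol does not propose a ranking.
- **A reader might infer that requests go uncaptured, because the Data collection list names only** "adequate completion (ie, ‘kit returned’ (yes/no)) and bowel cancer screening result (normal/abnormal") **and demographic items.** That list covers the screening system extract. Requests made during a call may be in the call record, and Outcomes refers to reopened episodes.

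**Conclusion.** The point holds as a minor one. Request and completion of a kit after a call do not confirm that the call addressed a barrier. That conclusion follows from the one-arm recording of barriers and the bundled content of the call, and needs no figure. The planning rates add only that background completion is not negligible: 21% to 24% of all PN-arm completions would be expected with text reminders alone, if the PN arm would otherwise have behaved like the text arm. The corresponding share among called people with a recorded barrier is unknown. The assumed scenarios above give about 6% to 24%, and a higher value is not excluded. The primary and secondary comparisons and the sample size of 901 per group are unaffected.

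**What to change.** In PN telephone calls, replace the claim of success and confirmation with a descriptive report.

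1. For each barrier discussed, give the number of people, the number requesting a kit after the call and the number completing one after the call. Show completions with and without a request, so that use of the original kit is visible.
2. State that the effect of addressing a given barrier is not estimable, because barriers are elicited in one arm only.
3. Show the text-arm completion proportion beside the table as context. Note that it is not a matched comparator: it covers everyone allocated to that arm and a different number of texts, whereas the barrier table covers only people who were called and reached.
4. Use call and request dates to separate requests made before the first call, which the week-13 text may have prompted, from those made after it.

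The cost is a change of wording and, if they are not already held, the dates of calls and requests. The downside is a weaker claim about barriers. No outcome, test or sample size changes.
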